### Treatment review

At each follow-up visit, participants will be reviewed by an ophthalmic clinician experienced in the management of FK. Clinical responses to antifungal therapy tend to be relatively slow (compared with bacterial infections). Prolonged topical treatment courses of 4–6 weeks are usually needed. Therefore, a change in therapy is usually not made for at least the first week. Other interventions may be indicated such as application of glue to corneal perforations, conjunctival flaps or TPK (corneal transplant).

### Stopping rules

If the study eye develops any serious adverse outcomes, the antifungal study medication may be discontinued if it is considered to be responsible for the adverse event. The patient will then be treated at the discretion of the supervising ophthalmologist, without breaking the randomisation code. If the medication is stopped, the patient will continue with the scheduled follow-up examinations.

### Lost to follow-up

Lost to follow-up rates are expected to be low, based on clinical experience. Participants who do not present for their follow-up visit will be contacted by telephone. Reasons for the lost to follow-up will be identified. Patients will be counselled about the importance of attending for ongoing treatment and monitoring. If they are unwell or unable to attend the hospital for some specific reason the study team will arrange to visit them in their home. Reasons for lost to follow-up will be recorded and reported.

### Data collection, management, confidentiality and access to data

Data will be collected using paper clinical record forms. These will be stored securely at SCEH and scanned electronic copies taken at the end of the day, stored on an encrypted drive with encrypted backups made daily both on and off-site. These data will be double entered into two separate MS Access databases. After double data entry has been completed data will be cleaned using EpiData V.3.1 software. Data entry is supervised by the local study coordinator on a daily basis, with data collection and data entry progress being reviewed by the study coordinator and chief investigator at LSHTM on a weekly basis. Data protection and confidentiality is maintained through restricted access to the database system and cupboard where the paper documents are kept. Only authorised users will have access to the locked filing cabinet. The database will be password protected, with each data entry staff member having their own password. Data exports for further analysis will be anonymised.

### Data and safety monitoring board

The data and safety monitoring board (DSMB) for this trial includes independent experts in bioethics, biostatistics, epidemiology and ophthalmology appointed by the trial steering committee and approved by the national regulatory authorities, before the start of the study. The DSMB meets at least twice each year and organises teleconferences as needed for progress reporting. The study protocol and modifications are subject to review and approval by ethics committees in Nepal and LSHTM, and by the DSMB. The DSMB will monitor any severe or unexpected events and oversees the data collected. The DSMB will be responsible for reviewing the results of the interim analysis and determining whether or not the trial should continue, with or without modifications.

### Monitoring for harm

Patients will be monitored at each visit for adverse events or reactions. We will follow standardised definitions for adverse events, adverse reactions, unexpected adverse reactions, serious adverse events or reactions, and suspected unexpected serious adverse reaction. These, along with the reporting scheme, are given in online supplementary appendix 2.

10.1136/bmjopen-2020-038066.supp2Supplementary data

### Biological specimens

The processing and analysis of biological specimens are detailed in online supplementary appendix 3.

10.1136/bmjopen-2020-038066.supp3Supplementary data

### Sample size considerations

The study is powered to test the hypothesis that CHX is non-inferior to NATA in terms of the primary outcome (BSCVA at 3 months) at a prespecified non-inferiority margin (Delta) of 0.15 logMAR units. It is possible that CHX is non-inferior to NATA, given pilot RCT data that showed no statistically significant difference between CHX and NATA, with a Cochrane review finding a non-significant trend favouring CHX over NATA.^10 18 19^ Despite this trend favouring CHX, we have chosen to carry out a non-inferiority trial rather than a superiority trial as this is a more clinically pragmatic approach. It would be counterproductive to conduct a superiority trial and find no statistically significant difference between the two treatments leading clinicians to potentially disregard CHX as a treatment, when in fact it may be ‘non-inferior’ to NATA, and be the only available or most cost-effective treatment.

The choice of delta: This clinically meaningful difference of 0.15 logMAR was chosen as a difference of 0.15 logMAR corresponds to approximately 1.5 lines on a Snellen chart; any difference greater than this is clinically significant, as a difference of less than 0.15 log MAR could potentially be accounted for by testing/retesting error.^29^ Furthermore, it was used in the MUTT1 trial, providing methodological consistency between studies.^6^ In addition, previous studies have suggested treated ulcers improve at a mean of four Snellen lines from baseline.

Sample size was calculated for 90% power and adjusted final alpha of 0.0492, taking account of a single interim analysis using O’Brien-Fleming approach to maintain type-1 error rate of 5%. A sample size of 452 is required to detect a non-inferiority margin of 0.15-logMAR in BSCVA 3 months after enrolment between arms, assuming 0.5 SD for 3 months BSCVA and 15% drop-out. However, given approximately 10% of infections are mixed and these will be excluded from the primary analysis, 500 patients will be recruited. This sample size provides 90% power to detect superiority in BSCVA at 3 months if there is ≥0.17 LogMAR units difference as a secondary analysis.

### Analysis plan

The analysis will be by intention to treat (ITT). All patient data will be analysed according to their randomisation allocation irrespective of whether or not the patient received or adhered to the allocated treatment. Consolidated Standards of Reporting Trials guidelines for analysing/reporting non-inferiority RCTs will be followed. A flow chart showing cases assessed, recruited and followed up by arm will be prepared.^32^ Baseline characteristics will be summarised by arm. The Standard Protocol Items: Recommendations for Interventional Trials checklist is given in online supplementary appendix 4.

10.1136/bmjopen-2020-038066.supp4Supplementary data

#### Primary outcome analysis: unadjusted analysis

The primary analysis will be conducted using all available data, missing data due to lost to follow-up will be excluded. The primary analysis of the primary outcome (BSCVA at 3 months) will be by linear regression, with treatment arm and baseline BSCVA as prespecified covariates. This controls for the baseline BSCVA. The treatment group is the primary predictor. Primary analysis will exclude mixed fungal and bacterial infection (isolated in the baseline sample).

We will use our alpha of 0.0492 to test the null hypotheses at 0.0492 significance. The null hypothesis for non-inferiority is that the mean BSCVA at 3 months for CHX is greater than or equal to 0.15 logMAR worse than the BSCVA when natamycin is used. Significance will be assessed using a two-tailed test at 0.0492 level for assessing non-inferiority. CHX will be non-inferior if the upper one-sided 95% confidence level for this regression coefficient (ie, the effect of CHX controlling for baseline BSCVA) exceeds 0.15 logMAR.

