#### Interim analysis

An interim analysis will be conducted for the DSMB by an independent statistician after 1/3 of patients recruited have completed follow-up.

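### The primary non-inferiority test is given two incompatible error rates (two-tailed 0.0492 and a one-sided 95% bound), and the 90% power holds on a one-sided reading but not under the two-tailed test

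*Protocol article*

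**What the plan says.** The places below are all in the protocol article.

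- **Sample size considerations.** "Sample size was calculated for 90% power and adjusted final alpha of 0.0492", with one O'Brien-Fleming interim analysis meant "to maintain type-1 error rate of 5" per cent. Neither figure is labelled one-sided or two-sided. "A sample size of 452 is required to detect a non-inferiority margin of 0.15-logMAR", at SD 0.5 with 15% drop-out. The target then rises to 500 because about 10% mixed infections leave the primary analysis. The section also claims 90% power for superiority at a difference of 0.17 logMAR or more.
- **Primary outcome analysis: unadjusted analysis.** "Significance will be assessed using a two-tailed test at 0.0492 level for assessing non-inferiority". The following sentence reads: "CHX will be non-inferior if the upper one-sided 95% confidence level for this regression coefficient" meets the stated relation to 0.15 logMAR. The model is a linear regression on arm and baseline BSCVA.
- **Interim analysis.** The look takes place "after 1/3 of patients recruited have completed follow-up".

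**The concern.** Consecutive sentences set two critical values for the trial's single confirmatory decision. A two-tailed test at 0.0492 puts 0.0246 in the tail that can declare non-inferiority, which is a 97.54% one-sided bound. A one-sided 95% bound puts 0.05 in that tail, about twice as much, and also drops the interim-adjusted alpha.

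Two things are at stake. First, a result whose upper limit falls between the two bounds is non-inferior under one sentence and not under the other. If the rule is not fixed, that choice could be made after the result is known. Second, the power statement matches only one of the two sentences, so a reader who takes the two-tailed test at its word is told 90% when the stated inputs give less.

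**Working it through.** **Inputs from the document:** margin 0.15; SD 0.5; power 90% (z = 1.2816); alpha 0.0492; drop-out 15%; mixed infections 10%; allocation 1:1; 500 recruited. **Assumption:** a true difference of 0. It is not stated, but it reproduces 452.

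**Step 1. Reproduce 452.** n per arm = 2 × 0.5² × (z_α + 1.2816)² / 0.15² = 22.22 × (z_α + 1.2816)².

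| Alpha in the relevant tail | z_α | n per arm | Evaluable total | After 15% drop-out |
|---|---|---|---|---|
| 0.0492 (one-sided 0.0492) | 1.653 | 191.3, so 192 | 384 | 384/0.85 = 452 |
| 0.05 (one-sided 95% bound) | 1.645 | 190.3, so 191 | 382 | 382/0.85 = 450 |
| 0.0246 (two-tailed 0.0492) | 1.967 | 234.5, so 235 | 470 | 470/0.85 = 553 |

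The first row is an exact match. The third, also allowing for mixed infections, would need 470/(0.85 × 0.90) = 614.4, or about 615 recruited.

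**Step 2. Power at the planned size.** Evaluable: 500 × 0.85 × 0.90 = 382.5. SE = 0.5 × √(4/382.5) = 0.0511. Power = Φ(0.15/0.0511 − z_α), with 0.15/SE = 2.934 before rounding.

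- One-sided 0.0492: Φ(2.934 − 1.653) = 90.0%
- One-sided 95% bound: Φ(2.934 − 1.645) = 90.1%
- Two-tailed 0.0492: Φ(2.934 − 1.967) = 83.3%

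With 384 evaluable the three figures are 90.1%, 90.2% and 83.5%.

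**Step 3. Effect of baseline adjustment.** If baseline and 3-month BSCVA correlate at r, the residual SD is 0.5 × √(1 − r²). The document gives no r, so these values are assumptions. Power of the two-tailed test at 382.5 evaluable is 83.3% at r = 0, 86.6% at r = 0.3, 90.0% at r = 0.43 and 92.2% at r = 0.5. The break-even value solves 1 − r² = 382.5/469.0 (469.0 is twice the unrounded 234.5 per arm), so r ≈ 0.43.

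**Step 4. Superiority statement.** The detectable difference at 90% power is (z + 1.2816) × 0.0511. Two-sided 0.0492 and two-sided 0.05 both give 0.166, which rounds to 0.17. One-sided 0.0492 gives 0.150. The superiority figure is therefore two-sided and the non-inferiority figure one-sided, and neither is labelled.

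**Step 5. Where the verdict changes.** The largest estimate (CHX minus natamycin) that passes is 0.15 − 1.967 × 0.0511 = 0.049 under the two-tailed sentence and 0.15 − 1.645 × 0.0511 = 0.066 under the one-sided sentence. At a true difference of 0, the estimate lies between them with probability 90.1% − 83.3% = 6.8%, about 7%.

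**The case against.** The best defence is that a one-sided test was meant throughout and that the word two-tailed is a slip. The exact match to 452 and the written confidence bound both point that way, and on that reading the 90% is right. This stands as far as it goes, and it rules out three stronger conclusions that a reader might draw.

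- *That the trial simply has 83% power.* It does not follow. The 83% depends on taking two-tailed literally and on no gain from the prespecified baseline covariate. The SD of 0.5 is described as that of 3-month BSCVA, not as a residual SD.
- *That 90% power holds only for one-sided 0.0492.* The written one-sided 95% bound gives 90.1%.
- *That the 0.17 shows 0.0492 was used two-sided.* Two-sided 0.05 fits equally well. A one-sided non-inferiority test beside a two-sided superiority test is no error in itself; the fault is the missing label.

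It is also fair that dropping the interim adjustment hardly matters numerically (z = 1.645 against 1.653; 450 against 452), and that the zone of disagreement is narrow, about 0.016 logMAR.

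The defence does not remove the contradiction. The two-tailed wording is explicit and is attached to non-inferiority by name. Nor is this a detail left to an analysis plan: an analysis plan could follow only one of the two sentences, and the protocol would still contain the other.

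**Conclusion.** Wrong as written. The primary test carries two incompatible error rates in the non-inferiority direction, 2.46% and 5%. The sample size follows a one-sided 0.0492, which has practically the same critical value as the one-sided 95% bound but not that of the two-tailed test.

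The stated 90% power is sound on either one-sided reading. It falls to about 83% under the two-tailed test, given SD 0.5, a true difference of 0, about 382 evaluable and no gain from baseline adjustment. The practical exposure is the band of estimates from about 0.049 to 0.066 logMAR in favour of natamycin, entered about 7% of the time when the arms are truly equal.

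The direction in which the decision sentence is worded (the bound exceeding 0.15) is a separate matter and carries no weight here.

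**What to change.** Before unmasking, state one rule and make the bound, the alpha and the power agree. Either of these would do:

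- **(a) Two-sided.** CHX is non-inferior if the upper limit of the two-sided 95.08% confidence interval for the treatment coefficient is below 0.15 logMAR. The same interval serves the superiority test. Restate power as about 83% without baseline adjustment, or as a range over assumed correlations (for example 83% at r = 0 to 90% at r = 0.43).
- **(b) One-sided.** Delete the word two-tailed, use a one-sided 95.08% upper bound below 0.15 logMAR, keep 90% power, and state openly that the overall one-sided type I error is 5%.

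Under either option, label the sidedness of alpha for non-inferiority and for superiority in the sample size section.

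The cost is wording. Option (a) makes the stated power less favourable; option (b) declares a one-sided 5% error. Neither needs extra patients. Holding 90% under (a) with no help from the baseline covariate would take about 615 recruited, so keeping 500 there means accepting the lower stated power.

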## Methods and analysis

### Trial design

We are conducting a single-masked, non-inferiority RCT comparing CHX 0.2% to natamycin 5% for the treatment of FK. The non-inferiority design of this trial offers a clinically pragmatic way to address this important question: if CHX is found to be within the prespecified non-inferiority margin of 0.15 logMAR (about 1.5 Snellen lines) then CHX may prove to be a sustainable solution for this aspect of the complex problem of FK.

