##### Analysis of other potential determinants for success

Logistic regression random-effects models will be used to analyse potential factors that may be associated with a poor primary outcome, BSCVA at 3 months, defined as >1.0 logMAR. Individual baseline characteristics will be used separately as an exposure variable with BSCVA at 3 months as the outcome, with the model adjusted for trial arm. A multivariate model will be built using parameters with a p<0.2 in the log likelihood ratio test. Variables will be removed one by one, by omitting the variable with the largest p value each time, until all predictors in the model have a p<0.05.

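### The non-inferiority decision sentence points the wrong way: it declares CHX non-inferior when the upper confidence limit is above 0.15 logMAR, not below it

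*Protocol article*

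**What the plan says.** The decision criterion is in the protocol article, Primary outcome analysis: unadjusted analysis. The primary model is a linear regression of 3-month BSCVA on treatment arm and baseline BSCVA. The condition for calling CHX non-inferior reads: "upper one-sided 95% confidence level for this regression coefficient (ie, the effect of CHX controlling for baseline BSCVA) exceeds 0.15 logMAR".

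Other parts of the article bear on how that sentence should read:

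- The null hypothesis, in the same paragraph, reads: "mean BSCVA at 3 months for CHX is greater than or equal to 0.15 logMAR worse than the BSCVA when natamycin is used".
- Trial design draws its favourable conclusion "if CHX is found to be within the prespecified non-inferiority margin of 0.15 logMAR". The strengths and limitations list says the same in similar terms.
- Sample size considerations gives a "prespecified non-inferiority margin (Delta) of 0.15 logMAR units".
- Analysis of other potential determinants for success fixes the direction of the scale by referring to a "poor primary outcome, BSCVA at 3 months, defined as >1.0 logMAR".

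**The concern.** On the logMAR scale a larger value is worse vision, so a positive CHX effect means CHX patients see less well than natamycin patients. The upper confidence limit is the largest disadvantage of CHX that the data still allow. Non-inferiority is shown when that largest plausible disadvantage is smaller than the margin. The article asks for it to be larger.

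Two results show the effect, taking a standard error of 0.051 (derived in the working):

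- An estimate of 0.20 logMAR worse has an upper limit of 0.20 + 1.645 × 0.051 = 0.284. The written rule calls this non-inferior.
- An estimate of 0.05 logMAR better has an upper limit of −0.05 + 0.084 = 0.034. The written rule does not call this non-inferior.

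The article says a recommendation to use CHX can follow from a non-inferior result, so the direction of this sentence decides the trial's main message. A published criterion that contradicts its own null also leaves the investigators open to the charge that they chose the direction after seeing the data.

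**Working it through.** **1. Direction of the test**

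Let d be the treatment coefficient, CHX minus natamycin, in logMAR.

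| Element | Where stated | In symbols |
|---|---|---|
| Scale | Determinants analysis: poor outcome is above 1.0 logMAR | d > 0 means CHX worse |
| Null | Primary outcome analysis | d ≥ +0.15 |
| Claim to be supported | Trial design: CHX within the margin | d < +0.15 |
| Valid rule | Follows from the null | upper limit of d < 0.15 |
| Rule as written | Primary outcome analysis | upper limit of d > 0.15 |

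The written rule is the complement of the valid one. Recoding the treatment variable does not help. If the coefficient were natamycin minus CHX, the valid rule would be that the lower limit lies above −0.15. An upper limit above +0.15 is not a valid criterion under either coding, and the article names the coefficient as the effect of CHX.

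**2. The article's own sample size**

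Inputs from Sample size considerations: margin 0.15, SD 0.5, power 90%, alpha 0.0492, drop-out 15%. Taking alpha as one-sided and the true difference as zero:

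- n per arm = 2 × SD² × (z₀.₉₅₀₈ + z₀.₉₀)² / margin² = 2 × 0.25 × (1.653 + 1.282)² / 0.0225 ≈ 191.4, rounded up to 192
- total = 384, and 384 / 0.85 = 452

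This reproduces the stated 452 exactly. Dividing by 0.90 for mixed infections gives 502, close to the stated 500. The formula is for a test that rejects when the upper limit is **below** +0.15, so the trial was sized for the opposite of the written rule.

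**3. Behaviour of each rule**

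- Evaluable patients (derived, not stated in the article): 500 × 0.85 × 0.90 = 382.5
- SE = 0.5 × √(4 / 382.5) = 0.0511
- Upper one-sided 95% limit = estimate + 1.645 × 0.0511 = estimate + 0.084
- This exceeds 0.15 when the estimate is above 0.15 − 0.084 = 0.066

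P(declare non-inferior), rule as written = 1 − Φ((0.066 − d) / 0.0511). The corrected rule gives one minus that.

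| True d (logMAR) | Rule as written | Corrected rule |
|---|---|---|
| −0.15 (CHX better) | about 0% | about 100% |
| 0 (equal) | 9.9% | 90.1% |
| +0.15 (at the margin) | 95.0% | 5.0% |
| +0.30 (CHX worse) | > 99.9% | about 0% |

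With a one-sided 0.0492 level the written rule gives 10.0% at equality and 95.1% at the margin. With one-sided 0.0246 it gives 16.7% and 97.5%. The reversal is present at every level.

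**The case against.** The strongest reply is that this is a one-word slip that nobody would act on. The null hypothesis just before the sentence is correctly directed and comes with a test level, so rejecting it is already a usable rule. The design section, the strengths list, the commitment to CONSORT non-inferiority reporting and the sample size all show what was meant. A competent statistician would notice. This stands as far as it goes: the intent can be recovered, and a reversed conclusion is unlikely in practice. It does not make the sentence right. This is the one place where the article turns the confidence limit into a verdict, and it contradicts the paragraph it sits in.

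The second reply is that the percentages are conditional. They assume literal use of the sentence, a derived evaluable number, and the unadjusted planning SD, although the primary model adjusts for baseline BSCVA. That is fair. For illustration, assume a correlation of 0.5 between baseline and 3-month BSCVA (the article gives none). The SE becomes 0.0511 × √(1 − 0.25) = 0.044, and the written rule then declares non-inferiority about 4% of the time at equality rather than 10%. The 95% at a true difference of 0.15 does not depend on the SE, and the direction of the error is unaffected.

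The wording cannot be put down to a damaged extraction or to detail left for an analysis plan. The sentence is complete and grammatical, and it states the rule wrongly rather than omitting it.

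**Conclusion.** The concern holds: the decision sentence is wrong as written and contradicts the article's own null hypothesis, design statement and sample size. If it were followed, the chance of declaring non-inferiority would be about 10% instead of 90% when the drugs are equal, and about 95% instead of 5% when CHX is worse by exactly the margin. These figures rest on SD 0.5, about 382 evaluable patients, a normal approximation and a one-sided 95% limit. The reversal itself rests on none of them.

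The most likely cause is a drafting slip. It must still be corrected, because it is the explicit threshold for the primary outcome.

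**What to change.** Replace the decision sentence, in the article's source protocol and in any analysis plan that repeats it, with wording such as:

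> CHX will be declared non-inferior if the upper confidence limit for the treatment coefficient (CHX minus natamycin, adjusted for baseline BSCVA; positive values mean worse vision with CHX) is below 0.15 logMAR.

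The same sentence should name a single confidence level. At present the paragraph says that "Significance will be assessed using a two-tailed test at 0.0492 level for assessing non-inferiority" and then uses a one-sided 95% limit. These are different levels: one-sided 0.0246 against one-sided 0.05. The stated 452 matches one-sided 0.0492, whereas one-sided 0.0246 would need 553 before the mixed-infection allowance. That choice is a separate matter, and the direction must be corrected whichever level is adopted.

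The cost is one sentence. Correcting the direction leaves 452 and 500 unchanged. The masking section has the analysis code prepared and tested before the allocation is released, so the correction should be made and dated before that release.
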